## Abstract

**Background:**

Livedoid vasculopathy is an orphan skin disease characterized by recurrent thrombosis of the cutaneous microcirculation. It manifests itself almost exclusively in the ankles, the back of the feet, and the distal part of the lower legs. Because of the vascular occlusion, patients suffer from intense local ischemic pain. Incidence of livedoid vasculopathy is estimated to be around 1:100,000. There are currently no approved treatments for livedoid vasculopathy, making off-label therapy the only option. In Europe, thromboprophylactic treatment with low-molecular-weight heparins has become widely accepted.

**Objective:**

The aim of this trial is the statistical verification of the therapeutic effects of the anticoagulant rivaroxaban in patients suffering from livedoid vasculopathy.

**Methods:**

We performed a therapeutic phase IIa trial designed as a prospective, one-armed, multicenter, interventional series of cases with a calculated sample size of 20 patients. The primary outcome is the assessment of local pain on the visual analog scale (VAS) as an intraindividual difference of 2 values between baseline and 12 weeks.

**Results:**

Enrollment started in December 2012 and was still open at the date of submission. The study is expected to finish in November 2014.

**Conclusions:**

Livedoid vasculopathy is associated with increased thrombophilia in the cutaneous microcirculation and the continuous use of anticoagulants helps improve the symptoms. The causes of cutaneous infarctions are heterogenous, but ultimately follow the known mechanisms of the coagulation cascade. Rivaroxaban affects the coagulation cascade and inhibits the factor Xa–dependent conversion of prothrombin to thrombin, thereby considerably reducing the risk of thrombosis.

**Trial Registration:**

Trial Registration EudraCT Number: 2012-000108-13-DE; https://www.clinicaltrialsregister.eu/ctr-search/search?query=eudract_number:2012-000108-13 (Archived by WebCite at http://www.webcitation.org/6UCktWVCA); German Clinical Trials Register (DRKS): DRKS00004652; https://drks-neu.uniklinik-freiburg.de/drks_web/navigate.do?navigationId=trial.HTML&TRIAL_ID=DRKS00004652 (Archived by WebCite at http://www.webcitation.org/6UCIAKyCS).

## Introduction

### Symptomatology

Livedoid vasculopathy is an orphan skin disease characterized by recurrent thrombosis of the cutaneous microcirculation [1-6]. The disease manifests itself almost exclusively in the ankles, the back of the feet, and the distal part of the lower legs [7-9]. Symptoms above the knee joints are rarely observed. An affection of viscera by this coagulation disorder has not been reported. Livedoid vasculopathy is difficult to diagnose due to a lack of pathognomonic markers [10-15].

Recurrent thrombus formation in the cutaneous microcirculation induces local skin necrosis and ulcerations (cutaneous infarctions) leading to irreversible atrophic scars (so-called atrophie blanche). Each cutaneous infarction inevitably leaves behind residual scar tissue, causing severe and continuous cutaneous damage in the lower extremities as the disease progresses. Typical clinical symptoms of livedoid vasculopathy are acute ulcerations and white scars (atrophie blanche), both of which appear concomitantly. In addition, the impaired blood flow caused by the disease and the accompanying reduction in oxygen saturation in the dermal microcapillaries causes a visible darkening of the skin and a vascular pattern corresponding to livedo racemosa [4,16].

Due to the vascular occlusion, patients suffer intense local ischemic pain (angina cutis). Furthermore, the acute ulcerations (cutaneous infarctions) and subsequent scarring in the ankle region lead to disfigurement of the foot and a severe reduction in patients’ quality of life.

### Epidemiology

Incidence of livedoid vasculopathy is estimated at around 1:100,000 [3,6]. The disease primarily affects young women, but it has also been observed in children. However, there is a significant lack of accurate epidemiological data and related patient registers. Livedoid vasculopathy fluctuates seasonally, with an exacerbation of symptoms in summer and temporary remission in winter. It is relevant to note that the estimated incidence includes patients with livedoid vasculopathy in the context of a vasculitis [17]. Based on diagnostic data from the clinics involved, it is possible to state that incidence of the prothrombotic (noninflammatory) vasculopathy described here is in fact lower than 1:100,000.

### Pathophysiology

The histological examination of skin samples in livedoid vasculopathy cases shows occlusive fibrinoid material on the vascular walls and in the lumen of dermal microcapillaries [1,2,7,8,11]. Unlike vasculitis, inflammatory leukocyte infiltration is not normally detected [4,5,18,19]. Blood vessel occlusion occurs primarily in the microcapillaries of the middle and upper dermis, which are essential for blood supply to the epidermis. Occlusion of these blood vessels leads to insufficient perfusion and supply of the dependent skin area and triggers a strong pain signal. Impaired blood blow (ischemia) leads to so-called angina cutis, which if untreated causes a cutaneous infarction [7]. Tissue death caused by the absence of blood flow is then visible as necrosis and ulceration of the foot skin. The exact physiopathological mechanism of livedoid vasculopathy remains unclear. However, analysis in specific cases of the increased blood coagulation and thrombosis associated with the disease has enabled the detection of known prothrombotic markers that could help explain the hypercoagulability. This has made it possible to observe a relation between livedoid vasculopathy and several prothrombotic coagulation defects, such as factor V Leiden gene mutation, protein C or protein S deficiency, prothrombin G20210A gene mutation, anticardiolipin antibodies, hyperhomocysteinemia, or antithrombin III deficiency [4,6,20-25]. Alterations of the fibrinolytic system have also been detected in livedoid vasculopathy patients, including increased plasminogen activator inhibitor-1 and/or lipoprotein(a) levels [13,14]. Although the aforementioned markers have been detected in cases of systemic hypercoagulability, it remains unclear why livedoid vasculopathy only affects the lower extremities and is not detected in any organs other than the skin. Furthermore, it is not possible to detect pathological coagulation parameters in all patients suffering from the disease; therefore, it is expected that additional, hitherto undetected mechanisms causing thrombus formation may exist [17,23].

### Treatment Options

There are currently no approved treatments for livedoid vasculopathy making off-label therapy the only option. Off-label treatment of livedoid vasculopathy seeks to prevent cutaneous microvascular occlusion, yet physicians treating the disease with anticoagulants are forced to rely on case reports and treatment series [13,20,26-30]. To date, the largest number of patients who have undergone documented treatment is 9 [31]. These patients were treated with immunoglobulins, which are nonspecific and multimodal. Immunoglobulins have an anti-inflammatory and immunomodulating effect, and it is assumed that they positively influence antibody-mediated activation of the coagulation system. This form of treatment has only been carried out at a reduced number of clinics and has not become standard practice in the treatment of livedoid vasculopathy [31,32].

Although the causes of thrombus formation are extremely varied, antithrombotic treatment is generally considered a promising area in the case of livedoid vasculopathy. However, it must be applied in the ischemic phase of the disease because the necrosis that follows this critical stage inevitably leads to irreversible scarring. In Europe, thromboprophylactic treatment with low-molecular-weight heparins (eg, enoxaparin 1-2 mg/kg body weight) has become widely accepted [28,33]. These drugs have been approved for the prevention and treatment of deep vein thrombosis. Coumarins have also been described in the literature as being helpful, and the successful use of fibrinolytics, rheological drugs, and immunoglobulins have also been reported by individual clinics [20,24].

### Therapeutic Benefits of Rivaroxaban

Rivaroxaban is a novel factor Xa inhibitor used for prophylaxis of thrombosis. Treatment with the investigational medicinal product (IMP) is expected to reduce pain, prevent disfiguring after-effects, and improve the general quality of life of those treated. Experience has proven that oral administration is clearly preferable to long-term treatment with daily subcutaneous injections of heparin necessary until now. In addition, although there is also an oral version of vitamin K antagonist Marcumar available, it requires constant international normalized ratio (INR) testing [20].

At the moment, only off-label treatments exist for livedoid vasculopathy. This means that physicians have to base their recommendations on reports of individual cases when treating livedoid vasculopathy patients. This study will provide physicians treating livedoid vasculopathy with empirical evidence for choosing the right therapy and set the basis for a possible indication expansion and inclusion in reimbursement lists.

At present, there is a delay of 5 years between the first appearance of symptoms and correct diagnosis of livedoid vasculopathy [4]. The results of this study may help other health professionals recognize and treat livedoid vasculopathy at an earlier stage. In addition, publication in scientific journals and presentation at congresses will stimulate scientific debate regarding the disease and possibly serve as a starting point for other studies.

### Therapeutic Risks of Rivaroxaban

The safety of rivaroxaban was tested in 8 phase III trials with a total of 16,041 patients who received the drug by the date of protocol submission [34].

Because of its pharmacological mechanism, use of rivaroxaban may be associated with an increased risk of occult or visible bleeding in any tissue or organ, which can lead to acute posthemorrhagic anemia. Signs, symptoms, and severity (including death) vary according to location and degree of bleeding or anemia.

In clinical trials, mucosal bleeding (eg, nosebleeds, gingival, gastrointestinal, and urogenital bleeding) and anemia were observed more frequently with rivaroxaban than with vitamin K antagonist treatment [34]. Therefore, monitoring of hemoglobin/hematocrit, in addition to adequate clinical observation, may be useful in detecting occult bleeding in certain cases.

The risk of hemorrhage is higher in certain patient groups, such as those with high uncontrolled hypertension. In addition, menstrual bleeding can increase in intensity and/or duration. Some complications associated with hemorrhage are general weakness, paleness, vertigo, headache, or inexplicable swelling, as well as dyspnea and sudden shock. In some cases, an anemia can cause symptoms of cardiac ischemia, such as chest pain (angina pectoris).

Known complications of severe bleeding, such as compartment syndrome and kidney failure due to hypoperfusion, have also been reported in patients receiving rivaroxaban. Therefore, it is important that patients being treated with anticoagulants be fully aware of the increased risk of hemorrhage associated with the treatment.

Reported adverse drug reactions related to rivaroxaban have been classified according to system organ class as per the Medical Dictionary for Regulatory Activities (MedDRA) and frequency in the summary of product characteristics.

### Disadvantages of Participating in the Study

The study-related disadvantages for participants are uncertainty regarding treatment success, additional time required for extra check-ups, additional time for surveys and tests, the need to register information daily in a patient diary, and answering of questionnaires.

### Study Aim

The aim of this trial is the statistical verification of the therapeutic effects of rivaroxaban in patients suffering from livedoid vasculopathy. In addition to effectiveness, the study will also take into account quality of life, patient safety, and the use of rescue medications.

## Methods

### Trial Design

This therapeutic phase IIa (proof of concept) trial is designed as a prospective, one-armed, multicenter, interventional series of cases without a statistical interim analysis and with a calculated sample size of 20 patients (2012-000108-13-DE; DRKS00004652).

### Primary Outcome

The primary outcome is the assessment of local pain on a visual analog scale (VAS): intraindividual difference of 2 values between baseline and 12 weeks.

### Secondary Outcome

In addition to the primary study goal, we checked for the following secondary outcomes:

Assessment of local pain on the VAS: intraindividual difference of values between baseline and 4 weeks.Assessment of local pain on the VAS: intraindividual difference of values between baseline and 8 weeks.Assessment of local pain on the VAS: intraindividual difference of average values over 2 weeks between the first and the last 2 weeks of the treatment.Assessment via the Dermatology Life Quality Index (DLQI): intraindividual difference of values between baseline and 4 weeks.Assessment (DLQI): intraindividual difference of values between baseline and 8 weeks.Assessment (DLQI): intraindividual difference of values between baseline and 12 weeks.Consumption of rescue medication: averaged over the week, listed for every week of treatment.Consumption of rescue medication: intraindividual difference of averaged values over 2 weeks between the first and the last 2 weeks of the treatment.

### Trial Population

It is assumed that all patients will have received some form of previous treatment for livedoid vasculopathy. For this reason, washout phases prior to the start of study treatment are defined in the inclusion and exclusion criteria.

Inclusion criteria preclude patients’ participation in other clinical studies during or within 30 days before inclusion in the present study. Study participants will be informed verbally regarding possible unforeseeable health risks and possible importation of bias into the study.

At the screening visit, patients will be asked about possible associations with the investigators or sponsor that might constitute a conflict of interest relationship of dependence (eg, relatives, employees). If a relationship of dependence is suspected, the patient cannot be included in the study.

Individuals described in § 40 Abs 4 und § 41 Abs 2 and 3 of the German drug law (Arzneimittelgesetz, AMG) are excluded from participation in the study.

Men and women will be included in this study. The expected ratio of male/female patients will be 1:3. No selection according to gender will take place for study inclusion.

### Inclusion Criteria

The following inclusion and exclusion criteria were defined:

Definite diagnosis of livedoid vasculopathy;Age ≥18 and <80 years;40 points on the pain VAS on at least 1 of the 7 days prior to treatment start;No participation in another intervention study within 30 days prior to treatment start;Adequate communication skills in the German language; andPatient must be able to recognize the nature, significance, and scope of the clinical trial and act accordingly.

### Exclusion Criteria

Known allergy to the trial medication;Known problems of galactose intolerance, lactase deficiency, or glucose-galactose malabsorption;Pregnancy;In women: insufficiently reliable contraception methods (requirement: Pearl Index <1);Lactation;Known renal impairment (creatinine clearance <30 mL/min);Known liver disease (Child-Pugh score B and C);Known ulcerative gastrointestinal disorders within 30 days before treatment start or during treatment;Uncontrolled, severe arterial hypertension (stage 3);Artificial heart valves;Acute pulmonary embolism;Bronchiectasis or pulmonary bleeding in the patient medical history;Known vascular retinopathy;Intracranial or intracerebral hemorrhage within 30 days before trial start or during trial;Brain, spinal cord, or eye surgery within the 30 days before trial start or during trial;Spinal/epidural anesthesia or puncture within 2 weeks before treatment or during trial;Administration of systemic heparin within 7 days before treatment;Use of nonsteroid antirheumatic (NSAR) drugs or platelet aggregation inhibitors within 7 days before treatment or during trial;Use of vitamin K antagonists (phenprocoumon, warfarin) and/or thrombin inhibitors (dabigatran) within 7 days before treatment or during trial;Concomitant administration of CYP3A4 inductors (eg, rifampicin, phenytoin, carbamazepine, phenobarbital, and St. John’s wort);Concomitant systemic treatment with azole antifungals (eg, ketoconazole, itraconazole, voriconazole, and posaconazole);Concomitant systemic treatment with human immunodeficiency virus (HIV) protease inhibitors (eg, ritonavir); andConcomitant systemic treatment with dronedarone.

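### Systemic heparin is the only look-back exclusion that is not also barred during the trial, so heparin added to rivaroxaban breaks no printed criterion

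*Protocol article*

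**What the plan says.** All references are to the protocol article. The Exclusion Criteria section contains seven items with a dated window before treatment or trial start. Six run on into the trial:

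- "Known ulcerative gastrointestinal disorders within 30 days before treatment start or during treatment"
- "Intracranial or intracerebral hemorrhage within 30 days before trial start or during trial"
- "Brain, spinal cord, or eye surgery within the 30 days before trial start or during trial"
- "Spinal/epidural anesthesia or puncture within 2 weeks before treatment or during trial"
- "Use of nonsteroid antirheumatic (NSAR) drugs or platelet aggregation inhibitors within 7 days before treatment or during trial"
- "Use of vitamin K antagonists (phenprocoumon, warfarin) and/or thrombin inhibitors (dabigatran) within 7 days before treatment or during trial"

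The seventh is "Administration of systemic heparin within 7 days before treatment", with nothing after it.

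Three other places bear on the consequences. End of Interventional Patient Treatment counts a patient as prematurely terminated if an inclusion or exclusion criterion is violated during the study. Statistics keeps such patients in the ITT population, does not replace missing values, and leaves the deviations that exclude a patient from the per-protocol set to the statistical analysis plan. Treatment Options says of the disease under study that "thromboprophylactic treatment with low-molecular-weight heparins (eg, enoxaparin 1-2 mg/kg body weight) has become widely accepted" in Europe.

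**The concern.** The heparin item has the same 7-day window as the two drug items that follow it, yet only those two continue during the trial. The list therefore bars other anticoagulants, antiplatelets and NSARs on trial but leaves out heparin, the anticoagulant that the article describes as customary for this disease.

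Bleeding safety is the main stake. Therapeutic Risks of Rivaroxaban treats bleeding, including fatal bleeding, as the drug's principal hazard. Risk-Benefit Analysis presents the exclusions and the limits on concomitant drugs as ways to reduce it. A second anticoagulant on top of rivaroxaban works against that aim.

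Attribution is a lesser stake. The trial has one arm and its primary endpoint is the change in pain from baseline to week 12, so relief from added heparin would be credited to rivaroxaban.

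**Working it through.** **1. Count.** Items in Exclusion Criteria with a window of the form *within … before*: 7. With a clause that extends them into treatment or trial: 6. Without: 7 − 6 = 1, systemic heparin. The undated pulmonary bleeding history is not a look-back window, and the 30-day rule on other studies is an inclusion criterion, so neither changes the count.

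**2. Does another section close the gap?**

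| Section | What it does | Bars heparin on trial? |
|---|---|---|
| Trial Population | Describes the pre-treatment windows as washout | No |
| Exclusion Criteria, items on concomitant drugs | Name CYP3A4 inductors, azoles, HIV protease inhibitors, dronedarone | No |
| Treatment Schedule | Raises the rivaroxaban dose if pain returns | No |
| End of Interventional Patient Treatment | Acts on violated criteria; allows withdrawal at the investigator's judgement | No rule on heparin |
| Risk-Benefit Analysis; Discussion of the Inclusion and Exclusion Criteria | Bar drugs that change rivaroxaban plasma concentration | Heparin not named |
| Compliance text after Ethical and Regulatory Aspects | Requires deviations to be documented and justified | Heparin not named as one |

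**3. The plan's sample size.** Inputs from Statistics: Δ/σ = 0.7, two-sided α = .05, power 80%, 20 evaluable patients. A paired t-test needs 18.03 patients. Dividing by 0.955, the efficiency of the Wilcoxon test under normality, gives 18.03 / 0.955 = 18.9, so 19. Simulated exact Wilcoxon power is about 80.5% at n=19 and 82.6% at n=20. The planned 20 is consistent with its inputs and leaves a margin of about one patient.

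**4. Power if week-12 values are lost.** Two-sided exact Wilcoxon signed-rank test, differences N(0.7, 1), rejecting when the smaller rank sum is at or below the critical value. Simulation error is about 0.1 percentage point.

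| Patients lost | n | Critical value | Power |
|---|---|---|---|
| 0 | 20 | 52 | about 82.6% |
| 1 | 19 | 46 | about 80.5% |
| 2 | 18 | 40 | about 77.9% |
| 3 | 17 | 34 | about 74.0% |

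**5. Effect of heparin on the primary test.** Assume no rivaroxaban effect, differences N(0, 1), n=20, and a gain δ (in SD) added to exactly k patients. The documents give neither k nor δ. The exact size at critical value 52 is 4.84%.

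| Heparin users k | δ = 0.7 | δ = 1.0 |
|---|---|---|
| 1 | about 4.8% | about 4.8% |
| 2 | about 5.3% | about 5.6% |
| 3 | about 6.2% | about 7.3% |
| 5 | about 9.5% | about 13.3% |

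One user leaves the rejection rate where it was, and two users move it by less than one percentage point. A visible inflation needs a quarter of the sample on heparin (5/20).

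**The case against.** The other side has a good case on several points.

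First, the heparin item does what Trial Population asks of it, which is to define a washout. That stands, but it does not explain the difference: the two neighbouring drug items have the same 7-day washout and are still barred on trial.

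Second, a reader might infer that the plan permits heparin during treatment. The documents do not support this. The regimen is fixed, returning pain is answered with more rivaroxaban, compliance with the protocol is mandatory, and the investigator may end participation. The source is also a journal article: it has no section on concomitant medication and does not name the rescue medication, and the full protocol may settle both. What can be said is that no printed criterion is broken, and that the printed window ends too early.

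Third, a reader might infer that the primary result is at risk of bias. With one or two heparin users the change is negligible, and larger numbers of users are assumed rather than documented. The article is also divided on heparin: Rationale for This Trial calls it effective, while Risk-Benefit Analysis says this has not been shown in clinical trials.

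Fourth, it is tempting to say that the correction costs the ITT analysis nothing. That does not follow. Once heparin on trial violates a criterion, the patient counts as prematurely terminated. The article does not say whether a week-12 VAS is then taken, and a missing value is not replaced. If heparin went mainly to patients whose pain persists (an assumption), losing them would remove poor responders and could favour rivaroxaban.

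**Conclusion.** The point holds as an inconsistency in the printed criteria: one of seven look-back exclusions lacks the clause that the other six carry, and no other section of the article supplies it. It is probably a drafting slip. Its weight comes from bleeding safety, because the omitted drug is an anticoagulant in common use for this disease and the comparable drugs are barred. The size of the safety risk cannot be given, since the documents state no rate of on-trial heparin use and such use is probably rare.

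The statistical consequence is secondary. The inflation figures rest on an assumed number of users, an assumed gain per user, and normal differences. The power figures rest on normal differences and the planned 0.7 SD. They show that losing one patient's week-12 value would keep power just above the planned 80%, and losing two would not.

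**What to change.** Extend the item "Administration of systemic heparin within 7 days before treatment" with the words *or during trial*, to match the items beside it. State as well that the week-12 VAS is still collected from any patient who receives heparin, so that the patient stays in the ITT primary analysis. Per-protocol handling can remain with the statistical analysis plan. If the omission was intended, give the reason instead.

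The cost is three words in one item, one sentence on follow-up, and possibly a few more patients counted as prematurely terminated. If the week-12 value is collected, the ITT test loses nobody. If it is not, the power losses shown in step 4 apply to the primary analysis.
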